# STUDY DESIGN

## Study Treatment and Duration of Treatment

This is two-arm randomized behavioral study to evaluate the feasibility, acceptability, and effectiveness of IMB counseling versus TAU in opioid-dependent naloxone recipient persons.

Sixty subjects will be enrolled in one of the following two study arms.

**Group 1**: IMB Counseling (REBOOT)

- - - Treatment arm participants will receive a single brief session of IMB counseling on overdose prevention at enrollment and months 4, 8, and 12.

**Group 2**: TAU

- - - Reference arm participants will receive TAU including referrals available to all participants.

## Treatment Discontinuation Criteria

There are no formal trial-stopping rules for this study. No formal interim efficacy analysis will be conducted.

If it becomes clear that the trial puts undue safety risk on study participants, outcomes are poor, or the trial will not achieve its enrollment goals, consideration will be given to stopping the trial, after consultation with the IRB and NIDA program officer (PO).

The overall safety risk to study participants will be determined through regular monitoring procedures. Safety issues will be evaluated as they arise; participants are given the pager number of the clinician on call which they can page in the event of an emergency or safety risk. Study clinicians will consult with [name], the medical director and Principal Investigator, on these safety issues on a case-by-case basis as they are reported by the participant. Non-urgent clinical issues that arise during the course of the study are discussed by the team’s research clinicians at the next weekly meeting with the PI [name]. During weekly meetings, study clinicians will review all the safety issues and incident adverse events (including lab abnormalities) for the study overall, by system category, and by possible relationship to the behavioral intervention. The PI will alert the NIDA PO immediately if at any point the team observes an unexpected frequency of serious Aes possibly related to the intervention.

# SUBJECT POPULATION

## Number of Subjects and Subject Selection

At least 60 subjects will be enrolled in this study, potentially up to 70, to ensure at least 60 people who inject drugs are included.

## Inclusion Criteria

Subjects must meet *all* of the following inclusion criteria to be eligible for participation in this study.

1. Age 18-65 years;
2. Current opioid dependence by SCID;
3. Urine positive for opioids during screening, excluding prescribed agonist maintenance therapy;

(4) History of prior opioid overdose;

(5) Previously received take-home naloxone;

(6) No serious illnesses likely to progress clinically during trial;

(7) Able and willing to provide informed consent, provide locator information, communicate in English, adhere to visit schedule.

## Exclusion Criteria

Subjects who meet *any* of the following exclusion criteria are not to be enrolled in this study.

(1) Suicidal ideation by SCID;

(2) Currently participating in another interventional research study that could possible impact the study’s outcomes of interest;

- 1. Any condition that, in the Principal Investigator’s judgment, interferes with safe study participation or adherence to study procedures.

# STUDY PROCEDURES

The study procedures to be conducted for each subject enrolled in the study are presented in tabular form in Appendix 1 and described in the text that follows. Additional information is provided in the study procedures manual.

The investigator will document any deviation from protocol procedures and notify appropriate regulatory authorities (e.g., IRB and/or NIH).

## Subject Enrollment and Treatment Assignment

In-person visits will occur at screening, enrollment, and every four months for 16 months.

## Pretreatment Assessments

### Screening Visit

Subjects will be screened within 30 days of enrollment to determine eligibility for participation in the study. The screening window can be extended to 42 days in exceptional circumstances. Subjects meeting all of the inclusion criteria and none of the exclusion criteria will return to the clinic within 30 days after screening for enrollment into the study.

Informed consent will be obtained at the beginning of the screening visit. After consent is obtained and eligibility is determined, a locator form is completed and HIPAA form is signed for substance abuse record retrieval and review of medical/criminal records. Screening visit will also include a clinical evaluation (Structured Clinical Interview for DSM-IV [SCID] for opioid dependence and suicidal ideation), blood-borne virus testing (rapid HIV/hepatitis C serology [if no confirmed serostatus] +/- CD4+ t cells & HIV viral load), and a urine toxicology test with expanded opioids.

Subjects will be compensated $10 for the screening visit.

### Enrollment Visit

Enrollment tests and procedures will be completed prior to enrollment and receipt of the first counseling session.

On the enrollment visit, participants will be randomized to receive the behavioral intervention (n=40) or TAU (n=20). **Randomization** will be 2:1 using permuted blocks of randomly selected sizes 3 and 6.

Participants will provide a urine toxicology test, and will undergo the baseline CAPI followed by initial counseling for the treatment group and TAU for the reference group. The next visit will be scheduled and participants will be compensated for their time.

Subjects will be compensated $30 for the enrollment visit.

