| 8.4.1. Primary Analysis | 24 |
| 8.4.2. Exploratory Analysis | 24 |
| 8.5. Sample Size | 24 |
| 9 RESPONSIBILITIES | 25 |
| 9.1. Investigator Responsibilities | 25 |
| 9.1.1. Good Clinical Practice | 25 |
| 9.1.2. Institutional Review Board (IRB) Approval | 25 |
| 9.1.3. Informed Consent | 25 |
| 9.1.4 Confidentiality | 26 |
| 9.1.5. Study Files and Retention of Records | 26 |
| 9.1.6. Case Report Forms (CRFs) | 26 |
| 9.1.7. Protocol Compliance | 27 |
| 9.1.8. Study Discontinuation | 27 |
| 11 APPENDICES | 28 |
| Appendix 1. Study Procedures Table | 29 |
| 12 REFERENCES | 30 |

PROTOCOL SYNOPSIS

San Francisco Department of Public Health

[name]

San Francisco CA 94102

| Study Title: | Repeated-dose Brief Intervention to Reduce Overdose and Risk Behaviors among Naloxone Recipients |
| --- | --- |
| IND Number: | N/A |
| Study Center(s) Planned: | 1 site in the United States |
| Number of Subjects Planned: | At least 60 subjects (60 who inject drugs, with up to 10 additional non-injecting subjects) |
| Target Population: | Opioid-dependent naloxone recipient adults who have overdosed |
| Duration of Treatment: | Subjects will be enrolled in trial for 16 months |

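### The protocol prints the full allocation rule (2:1, blocks of 3 and 6) for a single-site trial with visibly different arms, so the next assignment is partly predictable to anyone who has followed past ones

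*Protocol*

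**What the plan says.** The Enrollment Visit section of the protocol says that randomization "will be 2:1 using permuted blocks of randomly selected sizes 3 and 6", and the synopsis (Study Procedures/Frequency) has the same sentence. The planned arms are 40 REBOOT and 20 TAU. Total enrollment is described as "At least 60 subjects will be enrolled in this study, potentially up to 70".

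Other parts of the protocol bear on how far this rule can be exploited:

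- **One allocation stream.** The synopsis plans "1 site in the United States", and no stratification factor is named.
- **Different arms.** Under Study Treatment and Duration of Treatment, "Treatment arm participants will receive a single brief session of IMB counseling on overdose prevention at enrollment and months 4, 8, and 12", while "Reference arm participants will receive TAU including referrals available to all participants".
- **Blinding.** Section 5.4.2 states it for the CAPI interviewer. No other role is described as blinded.
- **Timing of entry.** Eligible people "will return to the clinic within 30 days after screening for enrollment into the study". The screening window may be extended to 42 days in exceptional cases.
- **Judgment in eligibility.** The last exclusion criterion covers any condition that, in the Principal Investigator's view, "interferes with safe study participation or adherence to study procedures".
- **Records.** Study Files and Retention of Records requires site source notes to include the treatment arm and the participant's start and end dates.

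**The concern.** Permuted blocks protect against selection bias only while the people who enroll participants cannot work out where they are in a block. The protocol is the document that site staff work from, and it gives them the ratio and both sizes. With one unstratified stream and arms that look different in practice, the remaining ingredient is knowledge of past assignments, which a small single-site team could plausibly have.

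If someone with that knowledge also influenced who entered next, people expected to attend could be placed preferentially in one arm. The by-arm visit completion rates, the Fisher and Wilcoxon tests and the log-rank test for dropout (Aim 1) would then partly reflect selection, as would the exploratory efficacy estimates. The Sample Size section says the exploratory results will be used, cautiously, in designing the full-scale trial. Its cautions concern imprecision and do not cover selection.

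**Working it through.** **Plan's own figures.** 60 × 2/3 = 40 and 60 × 1/3 = 20, which match the stated arm sizes.

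**Inputs.** From the protocol: ratio 2:1, block sizes 3 and 6 in random order, N = 60, one list. Assumptions: the two sizes are equally likely (the protocol gives no probabilities), and the observer knows every past assignment and updates exactly.

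**Start of the list, by hand.**

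- After REBOOT, REBOOT: this start has probability 2/3 × 1/2 = 1/3 in a block of 3 and 4/6 × 3/5 = 0.4 in a block of 6. The chance that TAU is next is (1/3 × 1 + 0.4 × 0.5)/(1/3 + 0.4) = 0.533/0.733 = 73%, against a nominal 33%.
- After one TAU: a TAU start has probability 1/3 in either size. The chance that REBOOT is next is (1 + 4/5)/2 = 90%, against a nominal 67%.
- After TAU, TAU: a block of 3 holds only one TAU, so the block must be 6 and the next four are certainly REBOOT.

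**Whole list, by simulation** (4,000 lists of 60 for sizes 3 and 6, exact Bayesian updating of the position in the block):

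| Target | Certain | Callable at ≥80% | Best guess correct |
|---|---|---|---|
| Next assignment | 10% (mean 6.1 of 60; 5th to 95th percentile 1 to 13) | 39% | 75% |
| Two ahead | 5.8% | 16% | 68% |
| Three ahead | 2.9% | 3% | 67% |

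Of the 10% that are certain, about 8 points are REBOOT and about 2 points are TAU (0.022 × 60 ≈ 1.3 slots). Always guessing REBOOT is right 66.7% of the time, so the gain for the next slot is (0.754 − 0.667) × 60 ≈ 5 extra correct guesses. Under simple 2:1 randomization nothing is certain and nothing is callable at 80%.

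**Sensitivity to the unstated size probabilities.** With P(size 3) = 1/3, 12% of next assignments are certain and the best guess is right 75% of the time. With P(size 3) = 2/3 the figures are 7% and 76%.

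**Alternatives, sizes still known to the observer (next assignment).**

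| Block sizes | Certain | Callable at ≥80% | Best guess correct |
|---|---|---|---|
| 3 only | 44% | 44% | 78% |
| 6 only | 29% | 34% | 74% |
| 3 and 6 (plan) | 10% | 39% | 75% |
| 6, 9 and 12 | 2% | 36% | 72% |

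Two ahead, sizes 6, 9 and 12 give a best guess of 69% and 20% callable at 80%, which is no better than the plan's 68% and 16%.

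**The case against.** The strongest case against has four parts.

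*The exploiting observer is hypothetical.* The protocol does not say who screens, books or randomizes, who holds the list, or whether anyone tracks past arms. A reader might infer that everyone except the CAPI interviewer sees each assignment, or that staff are in a position to steer participants toward REBOOT. The protocol supports neither. It names one blinded role, describes arms that differ in kind and requires arm to be recorded at the site. Visibility is therefore plausible but not stated, and nothing suggests intent. This stands.

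*The means are limited.* Eligible people are identified at screening and return later, so the judgment-based exclusion would normally be applied before the list position at randomization is known. The 42-day extension is exceptional. Steering by booking generally needs prediction beyond the next slot, and there the advantage nearly vanishes. This also stands and limits the practical risk, although it does not remove it when the enrolling person knows who is next.

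*Concealment may be covered elsewhere.* The protocol refers to a procedures manual, and a statistical analysis plan may exist. Silence about when an assignment is released is therefore not a finding. But no other document can undo the printing of the sizes in this one.

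*The consequence is narrow.* Aim 2 concerns the intervention arm, Aim 3 is a network association, and the overall rates in Aim 1 are not distorted by shifting people between arms. One TAU participant is 1/20 = 5 percentage points of completion. That shows how few controls there are and is not an estimate of bias. No bias has been estimated.

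**Conclusion.** The point holds as an avoidable vulnerability. The protocol discloses the complete allocation rule in two places of a single-stream trial with visibly different arms. With all past arms known and the two sizes equally likely, about 10% of next assignments are certain and about 75% can be guessed, against 67% without any information. Over the range of size probabilities examined these become 7% to 12% and 75% to 76%, so the conclusion does not depend on that assumption. It does depend on the observer knowing past arms, which is an inference.

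Random mixing of the two sizes already helps a good deal compared with a fixed block. Exposure is confined to the by-arm completion and dropout comparisons of Aim 1 and the exploratory efficacy estimates. The change is worth making because it costs almost nothing, not because the feasibility conclusions are in doubt.

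**What to change.** Delete the block sizes from the synopsis (Study Procedures/Frequency) and from Enrollment Visit. Say only that allocation is 2:1 in permuted blocks of randomly varying size. Hold the sizes in a document restricted to the person who generates the list. This costs two amended sentences and the usual IRB approval of an amendment.

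Deletion cannot undo what has already been read. If the list is not yet in use, regenerate it with a set of sizes that has not been disclosed. Larger mixed blocks, of which 6, 9 and 12 are one illustration, lower certain assignments to about 2% and correct guesses to about 72% even if the sizes leak. This second step is secondary: it removes only about (0.755 − 0.717) × 60 ≈ 2 correct guesses in 60, and it brings no gain two places ahead. Its cost is a new list and a slightly looser final split: 38 to 42 REBOOT among 60 in the simulations, compared with 39 to 41 under the present sizes.

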## Monthly Treatment Visits (Month 4, 8, 12 and 16)

Participant will be seen every 4 months.

At months 4, 8 and 12 participants will provide a urine toxicology test, complete the CAPI, and receive counseling for the treatment group and TAU for the reference group.

At month 16, participants will complete activities lists for the monthly visits in addition to completing the SCID and a blood-borne virus testing (rapid HIV/hepatitis C serology [if no confirmed serostatus] +/- CD4+ t cells & HIV viral load). REBOOT Participants will not receive counseling at month 16.

Subjects will be compensated as follows: $35 for month 4 visit, $45 for month 8, $55 for month 12, and $65 for month 16.

## Assessments

## Labs

Urine toxicology test (drugs of abuse screen/expanded opioids, including fentanyl) will be done each visit.

### 5.4.2. Computer Assisted Personal Interview (CAPI)

All participants will receive a CAPI at enrollment and months 4, 8, 12, and 16. The CAPI will **always** be conducted by a staffperson blinded to participant’s study arm and prior to administration of the REBOOT intervention or control arm procedures.

The CAPI includes demographic information (enrollment only), drug use history (enrollment only), extensive opiate overdose questions, drug use and drug-related risk behaviors, partner-by-partner data on injection/substance use/HCV status, quality of life scale (EQ5-D), Center for Epidemiologic Studies Depression Rating Scale, and Severity of Dependence Scale and participant satisfaction with treatment.

Primary and secondary outcome variables will be obtained from standardized scales assessed using CAPI to minimize underreporting of risk activities and enhance standardization.^4^ We will utilize the same overdose measures as in the pilot, which were developed in collaboration with other investigators (Drs [name], [name], [name], and [name]) to maximize comparability among overdose studies.

- **Quality of Life Surveys:** The quality of life scale included in this study is the EQ5-D. It will be completed by participants at enrollment and months 4, 8, 12 and 16 regardless of study arm. The Quality of Life Survey will be included in the CAPI.
- **Depression Rating Scale** The depression rating scale included in this study is the Center for Epidemiologic Studies Depression Rating Scale. It will be completed by participants at enrollment and months 4, 8, 12 and 16 regardless of study arm. The Depression Rating Scale will be included in the CAPI.
- **Severity of Dependence Scale:** The Severity of Dependence Scale will be completed by participants at enrollment and months 4, 8, 12 and 16 regardless of study arm. The Severity of Dependence Scale will be included in the CAPI.

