| Statistical Methods: | Specific Aim 1: To determine feasibility of a randomized trial with REBOOT, we will calculate screening and visit completion rates from the study database, with exact 95% confidence intervals (Cis), overall and by arm. Between-group differences will be assessed using Fisher’s exact and Wilcoxon ranksum tests. We will calculate Kaplan-Meier curves for time to dropout, by group, and test for differences using the log-rank test.  Specific Aim 2: To determine acceptability of REBOOT, we will calculate counseling completion rates from the study database by visit, and tabulate the proportions of active arm participants attending 0-4 counseling sessions. Via CAPI, we will inquire about participant satisfaction with the intervention and belief that it affected their drug use behaviors; responses will be presented as means, medians, or proportions, as appropriate, with 95% Cis.  Specific Aim 3: To evaluate the influence of egocentric social network characteristics on overdose events and naloxone use, we will use GEE Poisson models with robust standard errors to evaluate the association between network size, evaluated at baseline and each return visit, and numbers of experienced and witnessed overdose events in the same period; zero-inflated models will be used if needed. Results from this analysis will inform study design of a full efficacy trial and determine if randomization stratified by network size or targeted sampling strategies to ensure diversity in network size are needed. In addition, we will explore the influence of homophily and assortativity on experienced and witnessed overdose events using similar methods. Newman’s method will be used to calculate assortativity coefficients, a measure of the degree of demographic and risk behavior similarity within participants’ egocentric networks.  **Secondary analyses**: Exploratory analyses include preliminary efficacy estimates of REBOOT in decreasing overdose events (non-fatal or death), decreasing frequency of modifiable overdose / drug-related HIV risk behaviors, and increasing days of abstinence from illicit opioids and in substance abuse treatment.  Treatment effects on frequency of overdose events***.*** To determine if REBOOT, compared to TAU, reduces the risk of overdose among high-risk opioid users who have received take-home naloxone, as measured by the number of overdose events over 16 months. Overdose events will be determined by CAPI every 4 months via time-line follow-back of questions to determine the approximate date of non-fatal overdose that have proven reliable in multiple settings,^1-3^ with fatal episodes identified as above. We expect that repeated overdose events may be reasonably common in a subset of higher risk participants. To take advantage of this information, we will estimate treatment effects using Poisson models for the number of OD events in each reporting period, with robust standard errors to account for within-subject correlation and over-dispersion. |

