## Data Analysis

### Primary Analysis

Specific Aim 1: To determine feasibility of a randomized trial with REBOOT, we will calculate screening and visit completion rates from the study database, with exact 95% confidence intervals (Cis), overall and by arm. Between-group differences will be assessed using Fisher’s exact and Wilcoxon ranksum tests. We will calculate Kaplan-Meier curves for time to dropout, by group, and test for differences using the log-rank test.

Specific Aim 2: To determine acceptability of REBOOT, we will calculate counseling completion rates from the study database by visit, and tabulate the proportions of active arm participants attending 0-4 counseling sessions. Via CAPI, we will inquire about participant satisfaction with the intervention and belief that it affected their drug use behaviors; responses will be presented as means, medians, or proportions, as appropriate, with 95% Cis.

Specific Aim 3: To evaluate the influence of egocentric social network characteristics on overdose events and naloxone use, we will use GEE Poisson models with robust standard errors to evaluate the association between network size, evaluated at baseline and each return visit, and numbers of experienced and witnessed overdose events in the same period; zero-inflated models will be used if needed. Results from this analysis will inform study design of a full efficacy trial and determine if randomization stratified by network size or targeted sampling strategies to ensure diversity in network size are needed. In addition, we will explore the influence of homophily and assortativity on experienced and witnessed overdose events using similar methods. Newman’s method will be used to calculate assortativity coefficients, a measure of the degree of demographic and risk behavior similarity within participants’ egocentric networks.

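### The CAPI must be given by staff blinded to arm, yet it carries the questions about satisfaction with the intervention and its perceived effect, which puts that blind at risk from month 4 with no stated safeguard

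*Protocol*

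**What the plan says.** Section 5.4.2 sets two rules for the CAPI, without exception. It is to be "conducted by a staffperson blinded to participant’s study arm", and it is to take place "prior to administration of the REBOOT intervention or control arm procedures". The schedule is the same for both arms: "All participants will receive a CAPI at enrollment and months 4, 8, 12, and 16".

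The list of CAPI contents in section 5.4.2 ends with "Severity of Dependence Scale and participant satisfaction with treatment". The Synopsis (Study Procedures/Frequency) gives the same list. Section 8.4.1, Specific Aim 2, is more specific, and the Synopsis (Statistical Methods) repeats it: "Via CAPI, we will inquire about participant satisfaction with the intervention and belief that it affected their drug use behaviors".

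The interview is also the main source of outcome data. Section 5.4.2 states: "Primary and secondary outcome variables will be obtained from standardized scales assessed using CAPI". For the overdose count, the Synopsis (Statistical Methods) states: "Overdose events will be determined by CAPI every 4 months via time-line follow-back".

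**The concern.** The person who must not know the arm is the person assigned to ask about the intervention. The Protocol names no other staff member for these items, no self-completed part, no order of questions and no arm-neutral wording. It does not say whether TAU participants are asked them.

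Participants know whether they have been counseled, so bias from their own reporting cannot be removed by blinding staff. Interviewer blinding guards against something else: probing or recording differently by arm. That matters most for non-fatal overdose, where the interviewer walks the participant through dates, and it also applies to co-use, abstinence days, the RAB and the CES-D. If the blind is lost, the between-arm estimates of these outcomes become open to differential ascertainment. Under Sample Size, the Protocol says the exploratory results will be considered when the full-scale trial is designed, so both the estimates and the instrument could carry the weakness forward.

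**Working it through.** The Protocol gives no figure on this point to reproduce, so the check sets the provisions side by side.

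1. **Who asks.** Section 5.4.2: a blinded staff member conducts the CAPI at every visit. Specific Aim 2: the satisfaction and perceived-effect items are asked through the CAPI. Read together, the blinded interviewer asks them.

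2. **Who is asked.** Section 5.4.2 says that the EQ5-D, the CES-D and the Severity of Dependence Scale are completed in both arms. It makes no such statement for satisfaction. Specific Aim 2 concerns acceptability of REBOOT and tabulates session attendance in the active arm. Two readings remain:
   - *REBOOT only.* The appearance or absence of the items shows the arm directly.
   - *Both arms.* Participants rate either repeated 45-minute counseling or referrals, and say whether it changed their drug use. Answers and side remarks can readily show which.

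3. **Does the timing rule help?** Holding the CAPI before that day's procedures conceals only that day's session. At enrollment the order is that participants "will undergo the baseline CAPI followed by initial counseling for the treatment group and TAU for the reference group", so nothing has yet been delivered that could be disclosed or rated. By month 4 the enrollment session has taken place (Appendix 1), and the rule no longer protects the blind.

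4. **Which visits.** There are five CAPIs: enrollment and months 4, 8, 12 and 16. Removing enrollment leaves 5 − 1 = 4 follow-up interviews.
   - If the items come before the outcome questions, up to 4 of 4 are exposed.
   - If they come last, the outcomes of a given visit are recorded before that visit's disclosure. Exposure then arises only when the same interviewer sees the participant again: 0 of 4 if that never happens, and at most 4 − 1 = 3 of 4 (months 8, 12 and 16) if it always does.
   - Satisfaction is listed last, but the order of asking is not stated, and neither is the assignment of interviewers. The range of 0 to 4 cannot be narrowed from the Protocol.

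5. **Which results.**
   - *At risk:* the exploratory arm comparisons of interviewer-recorded self-report, namely non-fatal overdose, co-use, abstinence days, RAB and CES-D.
   - *Not at risk:* deaths (Vital Records and locator contacts), substance use treatment records, urine toxicology, and screening, visit and counseling completion from the study database. Specific Aim 3 relates overdose to network size, not to arm.

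**The case against.** **Disclosure is not inevitable.** A reader might infer that the two requirements cannot both be met, and that the CAPI necessarily unblinds the person who records every self-reported outcome. The Protocol does not support that. The contents list speaks of treatment in general, and the reference arm is itself called treatment as usual. A neutral scaled item put to both arms need not reveal anything. The enrollment interview comes before any counseling, and outcomes at a visit may be recorded before the items are reached. This objection stands and limits the point to a risk from month 4. It does not remove the point: Specific Aim 2 asks about the intervention and its effect, and no neutral wording or order is fixed.

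**The detail may be in the study procedures manual.** The Protocol refers to one, and it is not shown. It could settle order and wording. But a manual that gave these items to unblinded staff, or took them out of the interview, would depart from section 5.4.2 or from Specific Aim 2. The Protocol text itself has to change.

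**Other protections exist.** Standardized scales, time-line follow-back, urine tests and administrative records all limit the room for interviewer influence. That is correct, and blinding is not the only protection. None of them replaces it for self-reported non-fatal overdose or risk behavior.

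**The affected results are exploratory.** The primary objectives are feasibility, acceptability and network associations, and the Protocol expects little precision or power for efficacy and promises cautious reading. This stands, and it limits the consequence. Confidence intervals do not, however, show bias from unequal ascertainment.

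**A size for the bias is tempting but circular.** Assuming 10% under-recording of overdoses in REBOOT turns a true rate ratio of 1.00 into 1.00 × 0.90 = 0.90, but that only returns the assumption. Neither its size nor its direction comes from the Protocol.

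**Conclusion.** The conflict is real. As written, the Protocol has the blinded interviewer ask questions that are likely to reveal the arm from month 4 on, and it states no safeguard. Between none and all four follow-up interviews are exposed, depending on question order and interviewer assignment, neither of which is stated. The consequence is confined to the exploratory between-arm comparisons of self-reported outcomes, and its size cannot be derived. No primary conclusion rests on these comparisons. The point is still worth correcting because the remedy is specific and cheap, and the instrument may be reused in the full-scale trial.

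This rests on reading the CAPI as interviewer-administered throughout, as section 5.4.2 describes it, and on there being no separate handling of these items that the Protocol leaves unmentioned.

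**What to change.** Take the satisfaction and perceived-effect items out of the interviewer-administered part of the CAPI. Collect them by participant self-entry, or on a sealed self-completed form handled by neither the counselor nor the blinded interviewer. Specifically:

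- Open the module only after all outcome items of that visit are closed.
- Use it at months 4, 8, 12 and 16, and not at enrollment, where there is nothing yet to rate.
- State whether one or both arms receive it, hide the responses from the interviewer, and let no arm-dependent skip be visible to the interviewer.
- Amend section 5.4.2, section 8.4.1 (Specific Aim 2) and the two matching Synopsis entries (Study Procedures/Frequency and Statistical Methods).

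The counselor should not hand out the form. That would invite socially desirable answers on acceptability, which is a primary objective, and it does not fit the TAU arm or month 16, when no counseling is given.

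The cost is wording changes and one short self-completed module to handle. No visit or staff is added, and the Specific Aim 2 data are kept.
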